**4.3 Case criteria for discontinuation/ withdrawal**

4.3.1 Termination/ Withdrawal Decided by the Investigator

- During the clinical trial, the subject experiences other comorbidities, complications, or special physiological changes that make it inappropriate to continue the trial.
- The occurrence of SAEs or significant AEs makes it inappropriate for the subject to continue in the trial.
- The subject exhibits poor compliance, such as not taking the medication after enrollment, having no follow-up records, changing medication on their own, or using treatment drugs not specified in the protocol.
- The subject was mistakenly included in the trial despite not meeting the inclusion criteria.
- The subject meets any of the exclusion criteria.

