4.2.2 Exclusion criteria

- Known or suspected allergy to the experimental drug or its components;
- Use of prohibited drugs or other cognitive-enhancing drugs listed in the protocol after injury;
- History of severe head trauma, cerebrovascular accidents, or structural brain lesions;
- Conditions such as speech/ hearing impairment that prevent completion of cognitive function assessment;
- Occurrence of secondary brain injury after the current head injury;
- Need for craniotomy or external ventricular drainage;
- Concurrent serious injuries to other major organs or serious complications that may affect the subject's life;
- Patients with active epilepsy within the past year;
- Severe liver or kidney disease with abnormal liver or kidney function tests (alanine aminotransferase (ALT), aspartate aminotransferase (AST)) ≥ 3 times the upper limit of normal, serum creatinine (Scr) > upper limit of normal);
- Concurrent severe heart disease, lung disease, blood and hematopoietic system diseases, gastrointestinal diseases, or other severe or progressive systemic diseases;
- History or current diagnosis of malignant tumors (excluding cured stage IB or lower cervical cancer, non-invasive basal cell or squamous cell skin cancer; exclusion of breast cancer with complete remission (CR) > 10 years, malignant melanoma with CR > 10 years, and other malignant tumors with CR > 5 years);
- Presence of neurological or psychiatric disorders that prevent or unwillingness to cooperate;
- Pregnant, lactating women, or those with recent plans for childbirth;
- Investigator deems unsuitable for participation in the clinical trial;
- Participation in another clinical trial and use of experimental drugs in the last 3 months before the trial.

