4.3.3 Handling of Cases of Termination/ Withdrawal

For cases that terminate/ withdraw from the trial prematurely, researchers should take proactive measures to complete the last assessment as far as possible, to facilitate analysis of efficacy and safety. All cases of termination/ withdrawal should be documented in the electronic Case Report Form (eCRF), including a summary of the trial's conclusion and reasons for termination/ withdrawal.

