**13 Statistical Analysis of Datasets: Definition and Selection**

Full Analysis Set (FAS): The FAS operates under the Intention-To-Treat (ITT) principle, analyzing all cases that have been randomized into groups and have used the medication at least once. For cases where the entire course of treatment is not observable, the last observed data are carried forward to the final outcomes of the trial. According to the ITT principle, all patients are analyzed according to the groups into which they were randomized. This approach aims to maintain the benefits of randomization and to avoid biases that might arise from excluding patients who did not complete the treatment as originally planned.

PPS: The PPS consists of a subset of the FAS, generated from cases that have adhered closely to the trial protocol. This set includes all participants who completed the prescribed treatment and follow-up without any serious violations of the trial protocol. The precise definition of what constitutes a serious violation will be finalized during the data review process.

Safety Analysis Set (SS): The SS is used for the evaluation of safety and tolerability. It includes all participants who, after randomization, received at least one treatment and underwent at least one safety evaluation. In safety analyses, patients are analyzed based on the actual medication group they received, which helps in assessing the safety profile of the drug across different patient groups and treatment conditions. This dataset is crucial for identifying any potential adverse effects associated with the treatment.

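### Section 4.3 lets investigators withdraw randomised patients from the trial without saying that the Day 90 LOTCA is still collected, which works against the ITT aim and conflicts with Section 15.3

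*Protocol*

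**What the plan says.** Section 4.3.1 lists the grounds on which the investigator decides termination or withdrawal, treated as one event. Two of them, new complications and serious or significant adverse events, apply only where continuing in the trial becomes inappropriate. The other three carry no such condition:

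- "The subject exhibits poor compliance, such as not taking the medication after enrollment, having no follow-up records, changing medication on their own" (this ground also covers taking medicines outside those laid down for the study);
- mistaken enrolment: "The subject was mistakenly included in the trial despite not meeting the inclusion criteria";
- and, lastly, "The subject meets any of the exclusion criteria".

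The exclusion list in Section 4.2.2 includes "Occurrence of secondary brain injury after the current head injury" and "Need for craniotomy or external ventricular drainage".

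For patients who leave early, Section 4.3.3 says that "researchers should take proactive measures to complete the last assessment as far as possible", and that reasons be recorded. It sets no further visits.

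Section 13 keeps every randomised patient with at least one dose in the FAS, in the randomised group, and carries the last observation forward. Its stated aim includes "to avoid biases that might arise from excluding patients who did not complete the treatment as originally planned". Section 15.3 asks sites to step up follow-up of patients who respond poorly or miss medication.

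The primary endpoint (Section 7.1.1) is the LOTCA change from baseline to 90 days after treatment. The Trial Schedule places LOTCA at screening, end of treatment and Day 90 only.

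**The concern.** A patient who stops the drug or breaks a rule still has a Day 90 cognitive state, and an ITT comparison needs it. Section 4.3 gives a site grounds to end that patient's participation and never says that the Day 90 visit goes ahead. Whether the primary outcome is observed then depends on events after randomisation, such as compliance and other drug use, which treatment or its perceived failure can influence.

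Section 6.2 makes this sharper, because its drug prohibitions run through follow-up. A patient who received all 14 days of treatment and later takes an unlisted drug falls under Section 4.3.1. No study drug is left to stop, so withdrawal would achieve only the loss of the endpoint.

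The statistical analysis plan cannot settle this. It can choose how to handle missing values, but it cannot recover assessments that sites did not make.

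**Working it through.** **1. The passages side by side**

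| Question | Section 4.3 | Elsewhere |
|---|---|---|
| What happens to a poorly compliant patient? | Terminated or withdrawn (4.3.1) | Follow-up stepped up (15.3) |
| Is Day 90 LOTCA obtained after withdrawal? | A last assessment if possible (4.3.3) | Not addressed in 5.13 or the Trial Schedule |
| Is the patient analysed? | Not addressed | Yes, if dosed, with last value carried forward (13) |

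The first row is a conflict: Section 4.3.1 sets no threshold that tells a site when to withdraw and when to follow more closely. In the other two rows the patient is kept in the analysis while the outcome may be lost.

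**2. What is carried forward.** With three LOTCA time points, a patient withdrawn before the end-of-treatment assessment, and with no exit assessment, has only baseline and a carried change of 0. A patient withdrawn later carries the end-of-treatment change.

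**3. Planning figures (Section 10).** Mean changes are 26.0 for L-oxiracetam, 22.8 for oxiracetam and 20.0 for placebo. The difference from oxiracetam is 26.0 − 22.8 = 3.2, with SD 11.0. The stated 190 per group is close to reproduced: 2 × (1.96 + 0.8416)² × 11.0² / 3.2² = 185.5, so 186 (187 by exact t-test). With 236 per arm, power is 0.885. It would still be 0.83 if 15% of Day 90 values were simply dropped. The issue is therefore bias rather than power.

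**4. Illustration on assumed inputs.** The protocol gives no withdrawal rates by arm and no end-of-treatment LOTCA. Assume that a fraction w of an arm is withdrawn, that these patients would otherwise have had the arm's mean change m, and that the carried value is f × m. The arm mean falls by w × (1 − f) × m.

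- With f = 0 (baseline carried), each 1% withdrawn costs 0.01 × 22.8 = 0.23 to 0.01 × 26.0 = 0.26 points.
- A 5-point imbalance then shifts the difference by 0.05 × 22.8 = 1.14 to 0.05 × 26.0 = 1.30 points.
- With f = 0.5, the shift halves to 0.57 to 0.65.

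The resulting difference between L-oxiracetam and oxiracetam, planned at 3.2, is 3.2 − (1 − f) × (26.0 w_L − 22.8 w_O):

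| Withdrawn, L-oxiracetam / oxiracetam | f = 0 | f = 0.5 |
|---|---|---|
| 10% / 10% | 2.88 | 3.04 |
| 15% / 10% | 1.58 | 2.39 |
| 10% / 15% | 4.02 | 3.61 |

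**5. Where the sign reverses.** The table assumes that the withdrawn patient would have improved. If instead the patient deteriorates after the end-of-treatment assessment, the carried value exceeds the true Day 90 value and that arm's mean is overstated.

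**The case against.** Four points can fairly be made against the concern.

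- **The exclusion ground may be narrow.** It directly follows the ground on mistaken inclusion, and the pair reads naturally as ineligibility found late. New clinical events have their own grounds, which are conditional. A reader might infer that every patient with secondary brain injury or craniotomy after randomisation is removed, or that every serious adverse event ends participation. The text does not establish the first and contradicts the second. This objection stands. It does not touch poor compliance or unspecified drug use, which plainly arise after randomisation.
- **Nobody leaves the analysis.** Section 13 keeps dosed patients in the FAS, and its sentence on bias concerns exclusion from analysis. This stands against any claim that the ITT set is broken or that Section 13 is literally contradicted. It does not supply the missing Day 90 value.
- **The last assessment may mean Day 90.** It could be the final scheduled visit or an exit assessment. A reader might infer that outcomes are deliberately left uncollected, but Section 4.3.3 asks for proactive effort, so that goes too far. Still, the wording is ambiguous, applies only as far as possible and sets no schedule.
- **Some LOTCA scores cannot be had under any rule**, for example where speech or hearing is lost. True, and the fix must allow for it.

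**Conclusion.** The point holds as a gap and an inconsistency in trial conduct. Sections 4.3.1 to 4.3.3 allow withdrawal from the trial for post-randomisation reasons and do not secure the Day 90 LOTCA. That works against the purpose stated in Section 13 and conflicts with Section 15.3.

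Its size is not known. The 1.1 to 1.3 points would be 1.14 / 3.2 = 36% to 1.30 / 3.2 = 41% of the planned difference, and a reader might take this as the expected bias. The documents do not support that. It requires a 5-point imbalance between arms, baseline carried forward for all those patients, and an otherwise average recovery, none of which the protocol gives. The true shift may be smaller, absent or of the opposite sign. The case for acting rests on the cheap remedy and on the fact that uncollected outcomes cannot be repaired later.

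**What to change.** Reconcile Section 4.3 with Sections 13 and 15.3 by adding two statements to Section 4.3.3:

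1. Every randomised and dosed patient who stops study drug or deviates from the protocol, for whatever reason, remains on the Day 30, 60 and 90 schedule, including the Day 90 LOTCA where it can be done, unless consent is withdrawn or the patient is lost to follow-up.
2. For early stoppers, these visits are timed from the planned end of the 14-day treatment period. Section 5.13 counts from when medication ends, so a patient stopping on day 4 would be seen at 4 + 90 = 94 days, against 14 + 90 = 104 for a completer. Timing from the planned end measures all patients at the same time after randomisation.

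No change to the clinical grounds for stopping study drug is proposed. FAS membership needs no change either, since Section 13 already provides it.

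The cost is amendment wording and some extra effort to follow these patients. The visits are already in the schedule: telephone calls at Days 30 and 60, and one clinic visit at Day 90. The downside is that some off-treatment or post-deviation data enter the primary analysis, which is what the stated ITT aim implies.

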4.3.2 Withdrawal Initiated by the Subject

- The subject, unwilling or unable to continue with the clinical trial, requests withdrawal from the researcher. Various reasons for withdrawal include perceived lack of therapeutic effect, intolerance to certain adverse reactions, economic factors, or unspecified reasons. Efforts should be made to understand the reasons for withdrawal and document them accordingly.
- The subject does not explicitly request withdrawal but discontinues medication and testing, resulting in loss to follow-up.

4.3.3 Handling of Cases of Termination/ Withdrawal

For cases that terminate/ withdraw from the trial prematurely, researchers should take proactive measures to complete the last assessment as far as possible, to facilitate analysis of efficacy and safety. All cases of termination/ withdrawal should be documented in the electronic Case Report Form (eCRF), including a summary of the trial's conclusion and reasons for termination/ withdrawal.

**4.4 Criteria for Stopping the Trial**

Stopping a trial refers to discontinuing all trial activities before the planned end of the trial, primarily to protect the rights of the participants, ensure the quality of the trial, and avoid unnecessary financial losses. The criteria for stopping a trial include:

- If serious safety issues arise, the trial should be stopped promptly.
- If the drug is found to lack clinical value, the trial should be stopped to prevent delaying effective treatment for participants and to avoid unnecessary financial losses.
- Major errors in the clinical trial protocol are discovered, making it difficult to evaluate the drug's effects; or a well-designed protocol experiences significant deviations in implementation, complicating the assessment of the drug's effects.
- The sponsor requests termination (due to reasons like funding or management issues).
- The national regulatory authority mandates the trial's termination for any reason.

**5 Trial Procedures and Assessment Methods**

**5.1 Assessment Procedures**

The trial schedule is shown in “Trial Schedule”.

**5.2 Drug Provision**

- L-oxiracetam: Injectable L-oxiracetam, specification: 1g per vial, manufactured by Shenghe (China) Biopharma Co., Ltd.
- Oxiracetam: Injectable oxiracetam, specification: 1g per vial, manufactured by Shiyao Group Ouyi Pharmaceutical Co., Ltd.
- Placebo: Injectable L-oxiracetam or oxiracetam placebo with identical color, smell, and appearance but without active ingredients, manufactured by Shenghe (China) Biopharma Co., Ltd.

All investigational drugs will be provided by Nanjing Yoko Pharmaceutical Co., Ltd. in accordance with blinding requirements and meet quality standards.

**5.3 Drug Packaging and Labeling**

All study medications are assigned a specific drug number and are labeled accordingly. The external packaging of both the trial medication and the control medication is kept uniform. Each bulk package contains medication for 14 days plus an additional day.

Each package must be affixed with a label bearing the drug number. The label includes the approval number, drug number, drug name, indications, administration method, storage conditions, and the supplying entity of the medication, and is clearly marked with the phrase "For Clinical Research Use Only".

**5.4 Drug Storage and Stability**

Storage Conditions: Store in a cool (not exceeding 20°C), dry place, protected from light and sealed.

**5.5 Preparation of Formulations**

The trial medication is added by the research nurse to 100-250ml of 5% dextrose solution or 0.9% saline solution, shaken well, and administered intravenously at a standard rate without any special administration methods or rate requirements.

**5.6 Trial Period**

Screening period (-72h to 0h) + Treatment period (14+1 days) + Follow-up period of 90 Days.

**5.7 Trial Drug Accountability Procedure**

- All trial drugs are uniformly provided by the sponsor and transported to each clinical trial site according to the required storage conditions.
- Each clinical trial site appoints a dedicated person to manage the trial drugs (drug administrator). Upon receiving the drugs, the drug administrator should verify the following items before signing for them:
- Drug inspection report; ensure that the name, dosage form, specifications, batch number, and other information match the actual drug.
- Check whether the conditions during transportation conform to the storage requirements.
- Verify that the accompanying thermometer does not show any exceedance of limits. If it does, the sponsor must be notified immediately.
- Drug packaging: Inspect the outer packaging of the drugs to ensure it is intact and clearly labeled.
- Labels: Small bottles and large boxes must be labeled.
- The drug administrator will store the trial drugs separately and centrally according to their storage conditions. Daily temperature and humidity records must be kept during storage, and timely adjustments should be made when conditions exceed the specified ranges to ensure compliance with storage requirements.
- The drug administrator issues drugs to the research nurse based on prescriptions or orders from the research doctor, using drug codes, and accurately completes the drug dispensing/ collection log.
- After receiving the drugs, the research nurse stores them according to the trial drug storage conditions and prepares the drugs daily for use by the participants, without disclosing any specifics about the drugs to researchers or participants under any circumstances.
- The research nurse must hand over empty vials of injectables, any remaining drugs after use, and empty packaging directly to the drug administrator, and record this in the drug dispensing/ collection log.
- After the trial ends, the sponsor collects the remaining trial drugs (including those leftover by participants and those unused) for destruction by the sponsor itself.

**5.8 Trial Procedure Related Assessments**

- Demographic data: Includes age, gender, and ethnicity.
- Medical history: Inquiry or collection from existing medical records about the current condition of cranial injuries and any other diseases the participant might have, including medication and allergy history.
- Medication history: Inquire about prescription and over-the-counter drugs used prior to the administration of the trial drug, recording the generic name of the drugs, single dose administered, frequency, method of administration, and reasons for use.
- Disease diagnosis: Cranial injuries confirmed by CT or MRI scans (participants who have already been examined post-injury do not need to repeat the scans).
- Vital signs: Include body temperature, respiration, pulse, and blood pressure.
- Biological sample collection and laboratory assessment: Collection of blood and urine samples for routine blood tests, blood biochemistry, coagulation functions, liver and kidney function tests, TG, creatine kinase (CK) measurements, blood pregnancy tests, and routine urinalysis. Biological samples are to be collected, processed, and tested by the laboratories of the participating units. Before the receipt of trial drugs, clinical trial units must provide the sponsor with the normal reference ranges for each laboratory indicator and promptly inform the sponsor of any changes during the trial.
- 12-lead ECG: Heart rate and QT/ QTc interval results must be reported.
- Scale assessment: Use of the GCS to evaluate the severity of cranial injuries in participants, the MMSE, Montreal Cognitive Assessment (MoCA), and LOTCA to evaluate cognitive functions, the Glasgow Outcome Scale-Extended (GOS-E) to assess prognosis, and the Activities of Daily Life-the Barthel Index scale (ADL-BI) to evaluate improvements in post-injury living abilities of the participants. Detailed assessment scales and operating instructions are available in **Appendix 3**.

**5.9 Scale evaluation**

- Each research center must have at least one neurologist with professional experience in scale assessment to serve as a scale evaluator.
- Prior to the start of the trial, scale evaluators from each research center undergo training on the operation of scales. They must master the assessment methods of all scales used and pass a test on these methods before being issued a certificate of training completion.
- During their authorization period, scale evaluators are responsible solely for the assessment of participants using various scales and must not participate in any other research processes within the clinical trial.

**5.10 Clinical Laboratory Evaluation**

The laboratory evaluations include tests for routine blood work, blood biochemistry, coagulation functions, liver and kidney function, TG, CK, and urine analysis. The indicators to be tested are as follows:

- The laboratory test results obtained within 72 hours post-injury will be used as the entry criteria if multiple tests are conducted; the most recent test results closest to the end of medication use will be used for evaluation.
- Routine Blood Test: RBC, White Blood Cells (WBC), PLT count, and Hemoglobin (HGB) measurement.
- Coagulation Function: Prothrombin Time (PT), Activated Partial Thromboplastin Time (APTT), Thrombin Time (TT), and Fibrinogen (FIB).
- Blood Biochemistry: AST, ALT, Total Bilirubin (TBIL), Gamma-Glutamyl Transferase (γ-GT), Alkaline Phosphatase (ALP), Scr, Glomerular Filtration Rate (GFR), CK, and TG.
- The GFR is a derived indicator, calculated using the simplified MDRD：GFR [ml/ (min·1.73 m^2^)] = 186 × (Scr)^−1.154^ ×(age)^−0.203^ × (0.742 if female); When applying this formula, Scr must be measured in mg/ dl.
- Urine Test: Urine erythrocyte (ERY), Urinary leukocyte (LEU), Protein (PRO), and Glucose (GLU).
- Blood Pregnancy Test: All female participants of childbearing potential must undergo a blood pregnancy test.

These assessments ensure a comprehensive evaluation of the participants' health and safety during the trial, while also maintaining the integrity and reliability of the data collected.

**5.11 Screening Period (-72h to 0h)**

During this visitation window, the following tasks need to be completed and documented:

- Obtain written informed consent from the guardian and/ or participant.
- Clinical trial sites to assign screening numbers based on the order in which participant consent forms are signed.
- Researchers collect demographic data, medical history, and medication history, and perform vital signs checks on participants.
- Participants who have not undergone a CT or MRI scan post-injury should have one conducted.
- Collect blood and urine samples from participants to test for routine blood parameters (WBC, RBC, HGB, PLT), routine urine parameters (PRO, GLU, LEU, ERY), liver function (AST, ALT, TBIL, γ-GT, ALP), kidney function (Scr, GFR), coagulation function (PT, APTT, TT, FIB), CK, and TG. Conduct a 12-lead ECG and perform a blood pregnancy test in women of childbearing age. If these tests have been conducted post-injury already, they do not need to be repeated.
- Participants to complete the MMSE and the GCS for scale evaluation.
- Researchers to determine the suitability of participants for the trial based on collected information and test results, in accordance with inclusion and exclusion criteria.
- Participants to complete the MoCA and LOTCA for scale evaluation.
- Randomize participants into groups, assign drug numbers, and dispense treatment drugs.

